#### Correlation between radiological and pathological findings

In the intervention group, the correlation between radiological and pathological response will be assessed to determine the predictive value of CT scan in evaluating tumour response grade. Information from the post‐treatment CT scan will be compared to the pathological findings. In the control group, the diagnostic accuracy of CT scan will be estimated by comparing the radiological basal stage to the pathological report. Sensitivity, specificity, and positive and negative predictive values will be calculated.

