### Study objectives

The primary objective of this study is to determine if a therapeutic scheme based on NAC, surgery, and AC (Intervention group) increases the 2‐year progression‐free survival (PFS) compared to the standard treatment, based on surgery followed by AC (Control group) for LACC.

The secondary objectives are as follows:
To determine if the intervention group regimen increases 5‐year PFS compared to the control group.To determine if the intervention group increases 2‐ and 5‐year overall survival (OS) compared to the control group.To compare postoperative morbidity and mortality in both groups.To assess toxicity in both groups.To assess the therapeutic compliance rate in both groups.To assess the accuracy of the CT scan for the diagnosis of LACC in the control group.To assess the accuracy of the CT scan to evaluate tumour response after NAC in the intervention group.To validate the use of tumour response scales in CC.To determine if the addition of oxaliplatin impacts the pathological response in the group of patients over 70 years of age receiving NAC.

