### Eligibility criteria

#### Inclusion criteria

Clinical: (1) Histological confirmation of colon adenocarcinoma; (2) Age > 18 years for both males and females; (3) Good performance status (Karnofsky >60%, ECOG <2); (4) Blood analytics: haemoglobin >10 g/dL, leucocytes >3,0 × 10^9^/L, platelets >100.000 × 10^9^/L, glomerular filtration >50 mL/min, and total bilirubin <25 micromol/L; (5) Absence of chemotherapy contraindication and (6) Written and oral informed consent.

Radiological: (1) LACC: T4 or T3 with >5 mm extramural invasion on CT scan; (2) With or without nodal invasion on CT scan; (3) Absence of any distant metastases (M0) and (4) Radiologically resectable disease.

Therapeutical: All patients who undergo elective surgery with curative intention, regardless of the technique: open, laparoscopic, or robotic approach.

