### Patient identification and consent

All patients are evaluated at the time of diagnosis through medical history, physical examination, complete blood test with tumour markers, colonoscopy with biopsy and analysis of microsatellite instability. The patients are examined using a multidetector CT scan with oral and intravenous contrast. The standard CT acquisition protocol was performed in the venous phase and a section of 1.5 mm width was performed. This same protocol is employed for assessing the response in the interventional arm. In addition, a molecular determination is recommended but not mandatory: K‐N‐RAS and BRAF.

Potential candidates will be informed of the possibility of participating in the study verbally and in writing. Those who agree to participate (with written consent) and pass screening with the inclusion and exclusion criteria will be randomly assigned to one of the following treatment groups: (1) Intervention group: NAC + surgery + AC, or (2) Control group: Surgery + AC.

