### Randomisation

Centralised randomisation will be performed with a 1:1 ratio using a computer‐generated sequence. Patients will be randomised either to the interventional or control group after first obtaining their informed consent. Stratified randomisation is performed based on the radiological T and N stages into four groups: T3N‐, T3N+, T4N‐, and T4N+. The attending surgeon will then be informed of the patient's treatment group. When obtaining consent, the attending surgeon will not be aware of the assigned group, as the randomisation will be performed afterwards.

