Patient selection and their corresponding therapeutic strategy are determined by CT scan. Several studies suggest that preoperative staging has limited accuracy [38, 39, 40], whereas other support its impact on survival [41, 42]. A significant concern raised from the data collected in these studies is whether preoperative CT staging is accurate enough to avoid overtreatment for low‐risk patients who otherwise would not require NAC or AC. In the preliminary results of the FOxTROT study, only 7% of T2N0 tumours were misclassified [8], although, in the results, 24% of control patients did not meet the criteria for AC [25]. Meanwhile, a Spanish study evaluated the accuracy of CT after NAC, and over staging was observed in 9.1% of cases [43]. In another study published by Huh et al. with more than 500 patients, CT had accuracies of 79.1% and 73.3%, respectively, for T and N staging. Radiological staging was also found to be an independent predictor of long‐term survival and was recommended for selecting patients with CC participating in clinical trials with NAC [42]. Magnetic resonance imaging allows a better soft tissue discrimination and diffusion‐weighted imaging and may become an interesting complementary tool for the selection of patients [44].

Another drawback is the possibility of continued tumour growth despite neoadjuvant treatment. In the FOxTROT trial, 4.3% of patients that received NAC required emergency surgery due to obstruction during preoperative treatment [34]. According to a single‐arm randomised phase II study with 47 patients, none had progression while receiving CapeOX (oxaliplatin plus capecitabine) [45]. Consistent results were observed in another study with 65 LACC patients, with a tumour volume reduction of 62.5%, without any case of progression [14]. In patients that undergo surgery upfront, some factors may encourage the development of micrometastasis and tumour progression, such as the stimulation of growth factors associated with the procedure and immunosuppression during the early postoperative period. In a recent propensity score matching analysis, none of the patients experienced progression, and the incidence of distant recurrence was significantly reduced [46]. NAC could control these potential factors, thereby improving the efficacy of cancer surgery through local downstaging and elimination of circulating tumour cells, potential micrometastases, and lymph node metastases [46, 47].

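### For the control-group objective of diagnosing LACC, every patient is CT-positive by eligibility, so only the positive predictive value of CT can be estimated

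*Protocol article*

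**What the plan says.** Among the secondary objectives, the protocol article (Study objectives) lists: "To assess the accuracy of the CT scan for the diagnosis of LACC in the control group". The section on correlation between radiological and pathological findings gives the method: "In the control group, the diagnostic accuracy of CT scan will be estimated by comparing the radiological basal stage to the pathological report". It then closes with "Sensitivity, specificity, and positive and negative predictive values will be calculated".

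The radiological inclusion criteria begin with "LACC: T4 or T3 with >5 mm extramural invasion on CT scan". Nodal status is left open: "With or without nodal invasion on CT scan". Under Patient identification and consent, those who consent and "pass screening with the inclusion and exclusion criteria will be randomly assigned to one of the following treatment groups". The Discussion confirms the role of the scan: "Patient selection and their corresponding therapeutic strategy are determined by CT scan".

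The article describes no cohort of CT-negative patients with surgical pathology, and no correction for selection on the CT result.

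**The concern.** Sensitivity, specificity and negative predictive value all depend on patients whose index test is negative. Here the index test (CT showing LACC) is also the entry test, so those patients were never enrolled. An analyst who follows the stated objective and the stated list of measures would report figures fixed by the eligibility rule, whatever the true performance of CT.

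The risk is a misleading report. A published sensitivity of 100% would make CT look perfect as a selection tool, and a specificity of 0% would make it look useless; neither would be a finding. The Discussion names overtreatment of low-risk patients through inaccurate CT staging as a significant concern. The quantity that bears on it is the share of CT-positive patients whom pathology does not confirm, and the trial can estimate that.

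**Working it through.** The article states no figure for this analysis, so there is none to reproduce. The check is the 2x2 table for the control group.

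**Inputs**
- Target and population: LACC, control group (Study objectives).
- Index test: baseline CT. Reference: pathology report (Correlation between radiological and pathological findings).
- CT-positive at entry: all patients (Inclusion criteria; Patient identification and consent).
- Size: 119 per group, 5% dropouts (Statistical analysis and sample size calculation). 119 × 0.95 = 113.05, so about 113. Using the dropout allowance for missing pathology is an assumption.
- Share confirmed as LACC on pathology: not given. Assumed values from 60% to 100%.

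**Formulas**, with FN = TN = 0 imposed by eligibility
- Sensitivity = TP/(TP + FN) = TP/TP = 100%.
- Specificity = TN/(TN + FP) = 0/FP = 0%, or 0/0 if FP = 0.
- Negative predictive value = TN/(TN + FN) = 0/0, undefined.
- PPV = TP/(TP + FP), free to vary.

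**Results, n = 119**

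| Assumed confirmed share | TP / FP | Sensitivity | Specificity | NPV | PPV |
|---|---|---|---|---|---|
| 60% | 71 / 48 | 100% | 0% | undefined | 59.7% |
| 76% | 90 / 29 | 100% | 0% | undefined | 75.6% |
| 90% | 107 / 12 | 100% | 0% | undefined | 89.9% |
| 100% | 119 / 0 | 100% | undefined | undefined | 100% |

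The pattern is the same with n = 113.

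**Do the three fixed measures say anything about CT?** Take three hypothetical scanners in an unselected population and keep only the CT-positive patients, with PPV = se × prev / [se × prev + (1 − sp)(1 − prev)]:
- Sensitivity 80%, specificity 70%, prevalence 50%: 0.40/(0.40 + 0.15) = 72.7%.
- Sensitivity 90%, specificity 60%, prevalence 60%: 0.54/(0.54 + 0.16) = 77.1%.
- Sensitivity 60%, specificity 90%, prevalence 40%: 0.24/(0.24 + 0.06) = 80.0%.

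After selection, all three would be reported with sensitivity 100%, specificity 0% and undefined NPV. Only PPV differs.

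**Precision of PPV**, normal approximation, half-width = 1.96 × √[p(1 − p)/n]
- p = 0.60: n = 119 gives 1.96 × √(0.24/119) = 0.088; n = 113 gives 0.090.
- p = 0.90: n = 119 gives 1.96 × √(0.09/119) = 0.054; n = 113 gives 0.055.

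Wilson 95% intervals at n = 119 are 50.7% to 68.0% (71/119), 67.2% to 82.5% (90/119) and 83.2% to 94.1% (107/119).

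**Where the problem stops.** CT N+ and CT N- patients are both enrolled, as are CT T3 and CT T4. With invented counts for nodal status (TP 45, FP 25, FN 15, TN 34; total 119), sensitivity is 45/60 = 75.0%, specificity 34/59 = 57.6%, PPV 45/70 = 64.3% and NPV 34/49 = 69.4%. All four can be computed, but only among patients selected as CT-positive for LACC.

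**The case against.** The strongest reply is that the method section compares the radiological stage, not LACC yes or no, with pathology. Stage does vary among those enrolled: "Stratified randomisation is performed based on the radiological T and N stages into four groups", crossing T3 or T4 with N- or N+. The Discussion also cites CT accuracy for T and N staging separately. In addition, the sentence listing the four measures closes a paragraph that covers CT after neoadjuvant chemotherapy in the intervention group, and those findings are not fixed by eligibility. All of this stands. A reader might infer that the whole planned accuracy analysis is empty by construction; the article does not support that.

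It does not rescue the stated objective, which names LACC as the target in the control group. The radiological inclusion criteria attach that same label to the CT finding required for entry.

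A second reply is that LACC is not used uniformly: the Introduction describes it as stage III and high-risk stage II, the inclusion criteria by depth of invasion on CT. Under the Introduction's description, some CT T3N- patients might not count as index-positive, so the empty cells would no longer be guaranteed. That is fair, and it is a reason to state the target. But the only CT definition of LACC that the article gives is the inclusion criterion.

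A third reply is that the exact table can be left to a fuller document. The missing detail is not the complaint. The objective, population, measures and entry rule are all stated and do not fit together, and no analysis plan can recover CT-negative patients who were not enrolled.

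**Conclusion.** The point holds for one target: LACC as the inclusion criteria define it on CT, in the control group. Three of the four planned measures are then fixed or undefined through eligibility, and PPV alone is informative, with a 95% half-width of roughly 5 to 9 points for assumed PPVs of 60% to 90% and 113 to 119 patients.

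Three further inferences should be resisted:
- Specificity is not always 0%. It needs at least one overstaged patient; otherwise it is 0/0.
- The 24% of control patients in the FOxTROT trial who did not meet criteria for adjuvant chemotherapy, cited in the Discussion, is not an estimate of overstaging here. It measures a different condition, so 76% appears above only as one assumed value.
- The reference standard cannot be taken to be the CT criterion applied to the specimen. The article says only that CT is compared with the pathology report.

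Severity is moderate. This is one descriptive secondary objective; the primary progression-free survival analysis, the sample size and the randomisation are untouched.

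**What to change.** - Restate the control-group LACC objective as the PPV of CT, with an exact 95% confidence interval, and report its complement as the overstaging rate.
- State the pathological definition of LACC that serves as the reference, and reconcile the descriptions in the Introduction and the inclusion criteria. The choice is for the investigators.
- Drop sensitivity, specificity and negative predictive value for LACC.
- Report all four measures in the control group only for T4 versus T3 and N+ versus N-, labelled as conditional on selection by CT. Say how a pathological stage below T3 is counted in the T table.
- Leave the comparison of CT with pathological response after neoadjuvant chemotherapy as a separate analysis with its own named target.

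The cost is a change of wording before analysis. CT stage and pathology are already recorded, and PPV is already on the list, so no patients, visits or procedures are added. The trial gives up only a claim about CT sensitivity and specificity for LACC that its design cannot support.

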#### Postoperative morbidity and mortality

Postoperative morbidity and mortality will be graded according to the Clavien‐Dindo classification [22]. Transfusion requirements and long‐term outcomes will also be recorded, including incisional hernia and readmission. Chemotherapy toxicity will be recorded according to the CTCAE version 4.0.

### Statistical analysis and sample size calculation

Qualitative variables will be described using numbers and percentages. Quantitative variables will be described using the mean and standard deviation, or by median and interquartile range, for normally and distributed data, respectively. The Kolmogorov‐Smirnov test will be used to compare the normality of the variables. All randomised participants will be included in the population‐based intention‐to‐treat analysis. OS is defined as the time from surgery until death from any cause or follow‐up completion. PFS is defined as the time from the randomisation until local or distant recurrence or death.

PFS curves in the two treatment groups will be calculated using the Kaplan‐Meier method and compared using the Mantel Cox test. To determine the adjusted impact on OS and PFS, all clinically significant factors will be included in a Cox multiple regression model, and hazard ratio (HR) will be calculated with a 95% confidence interval. Statistical significance is set at *p* < 0.05. The SPSS version 15 software will be used for this purpose. Global statistical analysis will be performed by the main investigator.

This study is estimated to require 238 patients (119 per group, with a unilateral alpha type one error of 5%, power of 80%, and 5% of dropouts) to test the following hypothesis: Two‐year PFS of 75% and with an expected improvement of 15% in the neoadjuvant group, achieving a PFS of 90%.

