### Interventions

#### Intervention group

NAC will follow a scheme based on three cycles of XELOX (capecitabine 1000 mg/m^2^ days) 1–14 + oxaliplatin 130 mg/m^2^ on day (1) every 21 days, over the course of 9 weeks. Oncological surgery will take place 4 weeks after completing NAC. The XELOX scheme could be replaced by five cycles of FOLFOX, depending on the practice of each centre.

Given the inconclusive data on the addition of oxaliplatin in patients over 70 years old in the MOSAIC [17] and NSABP C‐07 studies [18], in this subgroup of patients or in those with some comorbidities which limit the use of oxaliplatin, such as nephropathy, three cycles of capecitabine alone could be used instead exceptionally.

AC will start 4–6 weeks after surgery based on five cycles of XELOX, according to the initial clinical staging. If this interval is exceeded, the use of complementary therapy is left to the researcher's discretion.

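### Overall survival is timed from surgery, a post-randomisation event that depends on the arm, so the OS comparison is not a randomised one and leaves out the neoadjuvant period

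*Protocol article*

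**What the plan says.** Three consecutive sentences in the protocol article, Statistical analysis and sample size calculation, bear on this point:

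- Population: "All randomised participants will be included in the population‐based intention‐to‐treat analysis".
- OS: "OS is defined as the time from surgery until death from any cause", or until follow-up ends.
- PFS: "PFS is defined as the time from the randomisation until local or distant recurrence or death".

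Under Intervention group, three XELOX cycles are given "over the course of 9 weeks", and then "Oncological surgery will take place 4 weeks after completing NAC". A substitution is allowed: "The XELOX scheme could be replaced by five cycles of FOLFOX, depending on the practice of each centre". The length of a FOLFOX cycle is not given.

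Under Patient identification and consent, the control sequence is surgery and then adjuvant chemotherapy. No interval from randomisation to surgery is stated.

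Study objectives lists OS at 2 and 5 years as a secondary comparison between the arms. The statistical section also names OS, with PFS, as an outcome for the adjusted Cox model. The article gives no other origin for OS and no rule for patients who never reach surgery.

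**The concern.** Randomisation makes the arms comparable at the moment of allocation. Surgery happens later, and both its timing and whether it happens at all can depend on the allocated arm. A clock that starts at surgery compares patients who have survived to, and undergone, an operation. These are not the groups that were randomised.

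Three consequences follow.

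- A patient who dies before surgery, or is never operated on, has no OS start time. The promise to analyse everyone randomised cannot then be kept for OS as defined.
- The same pre-operative death is an event for PFS but does not exist for OS.
- A fixed landmark such as 2 years falls at a different time since randomisation in each arm.

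The NAC period lies wholly outside the OS clock. The Introduction itself raises tumour growth during NAC, local complications and metastatic spread as concerns about the strategy, and the abstract says the trial will show whether the sequence improves survival. An OS that begins after NAC does not cover that part of the question.

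**Working it through.** The article states no OS figure to reproduce. The check covers the offset between randomisation and the OS clock, and how many deaths could fall inside it.

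**Inputs from the article.** NAC: 3 cycles of 21 days = 63 days (9 weeks). End of NAC to surgery: 4 weeks = 28 days. Group size: 119 per arm.

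**Assumptions (not in the article).** NAC starts at randomisation and XELOX is given as scheduled. The control wait for surgery is 2 to 6 weeks. OS at 2 years is 85 to 95%, with a constant hazard. One month is 30.4375 days.

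**Step 1: offset.**
- NAC arm: 63 + 28 = 91 days = 13 weeks; 91 / 30.4375 = 2.99 months.
- Control arm: 14 / 30.4375 = 0.46 months, up to 42 / 30.4375 = 1.38 months.
- Difference in origin between arms: 13 − 2 = 11 weeks, down to 13 − 6 = 7 weeks.

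**Step 2: when 2-year OS is read, counted from randomisation.**
- NAC: 24 + 2.99 = about 27.0 months.
- Control: 24 + 0.46 = about 24.5 months, up to 24 + 1.38 = about 25.4 months.

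**Step 3: deaths before the clock starts (illustration).** With S the 2-year OS, hazard λ = −ln(S)/24 per month. Expected deaths before surgery = 119 × (1 − exp(−λd)), where d is the offset in months. For example, at S = 0.90 in the NAC arm, 1 − exp(−λ × 2.99) = 0.0130, and 119 × 0.0130 = 1.6.

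| Assumed 2-year OS | NAC, 13 weeks | Control, 2 weeks | Control, 4 weeks | Control, 6 weeks |
|---|---|---|---|---|
| 85% | 2.4 | 0.4 | 0.7 | 1.1 |
| 90% | 1.6 | 0.2 | 0.5 | 0.7 |
| 95% | 0.8 | 0.1 | 0.2 | 0.4 |

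Patients who survive but are never operated on would add to the number without an OS start time. The article gives no rate for them, so none is assumed.

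**Step 4: does Step 3 measure bias?** No. Under a constant hazard S(t) = exp(−λt), so S(27)/S(3) = S(24). If every survivor is operated on, 2-year OS from surgery equals 2-year OS from randomisation: the deaths lost in the first 3 months are balanced by those picked up between months 24 and 27. Bias needs something more, such as a hazard that changes over time, excess early deaths from treatment, or patients never operated on.

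**The case against.** The strongest reply is that no bias has been shown, and on size and direction that reply stands. At 90% 2-year OS, about 1.6 of 119 × 0.10 = 11.9 expected 2-year deaths in the NAC arm, or 13%, fall before the clock starts. A reader might take this as a measure of bias, but Step 4 shows that it is not.

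A reader might also infer that the definition favours NAC. The documents do not settle this. Dropping early failures favours NAC, while reading NAC survival later after randomisation works against it.

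Nor are patients lost from the NAC arm only. Controls also wait for surgery and can die or go without resection, over what is probably a shorter window. Eligibility requires radiologically resectable disease, which limits such losses. The patients with obstruction during NAC in the earlier trial cited in the Discussion had emergency surgery, so they would have a surgery date and are no evidence of loss.

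It is also fair to say that the exclusion of unoperated patients follows from the definition and is not written down. The full protocol could hold a rule for them. A condensed article can leave out such a rule without fault. Here, however, the article states the time origin itself, and a rule for missing surgery dates would not undo an arm-dependent origin for everyone else.

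Finally, OS is one of several secondary outcomes. The article does not call it key, and it names Kaplan-Meier curves and the Mantel-Cox test for PFS only. That limits the reach of the point but does not answer it, because OS at 2 and 5 years remains a declared comparison between arms with a planned Cox model.

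**Conclusion.** The point holds. As defined, OS starts at a post-randomisation event that depends on the arm. It conflicts with the intention-to-treat sentence and with the origin used for PFS, so the 2- and 5-year OS comparison is not a true randomised comparison and omits the NAC period.

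The firm part of the size is the offset: 13 weeks from the start of NAC under XELOX. Any wait before NAC would lengthen the time from randomisation, emergency surgery would shorten it, and FOLFOX may shift it. The landmark difference (about 27 months against 24.5 to 25.4 months) also rests on the assumed control wait. The counts of deaths before the clock starts rest on an assumed constant hazard and assumed OS levels; they show how many events could go uncounted and nothing about net bias.

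The primary endpoint is correctly timed from randomisation, and the sample size of 238 rests on PFS, so neither is touched.

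**What to change.** Define OS as the time from randomisation to death from any cause, censored at the date last known alive, in all randomised patients in both arms. Read 2- and 5-year OS at 24 and 60 months from randomisation. If survival from surgery is of clinical interest, label it descriptive and keep it out of the between-arm inference.

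This costs one sentence in the protocol and the analysis plan. It needs no new data, since randomisation is central and PFS already uses its date, and it leaves the sample size unchanged. It should be settled before OS is analysed: the trial is open label and the main investigator performs the overall analysis, so an origin chosen after results are seen would be hard to defend.

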## INTRODUCTION

Colon cancer (CC) is a public health problem due to its high prevalence and increasing incidence in younger patient populations [1]. It is the leading cause of cancer‐related death among males aged 20–49 years, with an ascending trend in young women in the USA [2].

Based on current clinical practice, the mainstay treatment for locally advanced CC (LACC) (stage III and high‐risk stage II) is oncological surgery followed by adjuvant chemotherapy (AC), which aims to decrease the risk of locoregional and distant relapse and increase overall survival (OS) [3]. Based on previous experiences with other locally advanced gastrointestinal tumours, neoadjuvant chemotherapy (NAC) is a relatively new concept in the treatment of LACC [4, 5, 6].

There are several potential advantages of NAC in LACC, such as reduced tumour cell‐shedding during surgery, increased likelihood of R0 resection, reduced number of positive lymph nodes, control of systemic metastatic spread, and the ability to test tumour chemosensitivity in vivo [7, 8, 9, 10]. Furthermore, the use of NAC is independent of eventual surgical complications, thus avoiding AC delays and improving chemotherapy completion rates.

Theoretically, however, NAC might increase perioperative complications and mortality rates. It has been a concern that tumour growth during NAC, in the case of poor tumour response, could lead to local complications, such as bowel obstruction or perforation requiring emergency surgery or even metastatic disease development. Furthermore, over staging by current imaging methods may lead to the overtreatment of low‐risk patients [8].

Several studies have demonstrated the safety and efficacy of NAC, but a survival benefit is still unclear [11, 12, 13, 14]. NAC has recently been added to the American guidelines from the National Comprehensive Cancer Network (NCCN) as an alternative for selected LACC cases (TNM‐T4b tumours) [15], based on studies that revealed a significantly improved survival rate [7]. Therefore, it is of great interest to explore the potential benefit of neoadjuvant therapy in LACC, analysing whether the tumour's response translates into a survival benefit.

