### Outcome parameters

The primary outcome of this trial will be 2‐year PFS. Follow‐up will be performed by Oncology and General Surgery Services, as per usual practice. During the first 2 years, a physical examination and assessment of tumour markers will be done every 3 months, whereas a thoracic‐abdominal‐pelvic CT scan will be performed every 6 months. One year after surgery, a colonoscopy will be performed. If no lesions are identified, repeat colonoscopy will be done after 5 years. If polyps are identified, then it will be requested after 2‐years. From the third to fifth postoperative year, physical examination, tumour markers, and CT scan will be performed every 6 months.

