### Secondary outcome analysis

#### Tumour response grade

In the intervention group, the tumour response grade assessment will be radiologically assessed 3 weeks after NAC finishing by comparing pre‐ and post‐treatment TNM, tumour volume, and also according to the RECIST criteria [20]. Moreover, the pathological tumour response will be recorded, employing a modified Ryan scale, which is commonly used in rectal cancer [21].

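### The primary PFS definition starts at randomisation but counts only recurrence or death, so disease failure before or at surgery is not an event in either arm; omitting preoperative progression tends to favour the neoadjuvant arm, by an amount the document cannot settle

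*Protocol article*

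**What the plan says.** Under Outcome parameters: "The primary outcome of this trial will be 2‐year PFS". Under Statistical analysis and sample size calculation: "PFS is defined as the time from the randomisation until local or distant recurrence or death". The same section keeps all randomised participants in an intention-to-treat analysis and plans for 2-year PFS of 75% in control and 90% with NAC, 119 patients per group.

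The Intervention group section gives NAC "over the course of 9 weeks. Oncological surgery will take place 4 weeks after completing NAC". Under Tumour response grade, in the intervention group only, "the tumour response grade assessment will be radiologically assessed 3 weeks after NAC finishing".

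The Introduction states the concern that "tumour growth during NAC, in the case of poor tumour response, could lead to local complications", and extends it to emergency surgery and new metastases. The Discussion returns to continued growth under NAC as a drawback. No section says how a patient who progresses before surgery, or is not completely resected, is counted in PFS.

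**The concern.** The endpoint is called progression-free survival, but progression is not in its event list. A recurrence-or-death list suits patients who enter a trial already resected. Here they enter with the tumour in place, and entry requires radiologically resectable disease, so losing resectability is a change after randomisation.

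Under intention to treat, a patient whose primary grows or becomes unresectable stays in the analysis and is event-free until a recurrence or death is recorded. Both arms have this gap, but only the NAC arm has a planned treatment period before surgery. The definition therefore leaves out a failure that the document itself names as a concern for the experimental strategy. It matters because few NAC events are expected, so a handful of patients can change the primary comparison. The trial is also open label, so if counting is left to case-by-case judgement, those judgements would be made with the arm known.

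**Working it through.** **Inputs**

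- 119 per group; 2-year PFS 75% and 90% (Statistical analysis and sample size calculation).
- 9 weeks of NAC, surgery 4 weeks later (Intervention group); CT 3 weeks after NAC ends (Tumour response grade).
- No progression under preoperative chemotherapy in cited series of 47 and 65 patients (Discussion). A propensity-matched series, also with none, is cited without its size.
- Emergency surgery for obstruction during NAC in the cited phase III trial: 4.3%. Free margins in that trial: 94% with NAC, 89% in control (Discussion).

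**1. The preoperative window.** 9 + 4 = 13 weeks from the start of NAC to surgery. The restaging CT falls at 9 + 3 = 12 weeks, about one week before surgery. The article gives no control-arm waiting time, but that arm has no treatment phase before surgery.

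**2. Planned events by 2 years, ignoring dropout.**

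- NAC: (1 − 0.90) × 119 = 11.9.
- Control: (1 − 0.75) × 119 = 29.8.

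**3. Weight of one uncounted NAC patient.** 1/119 = 0.84 percentage points of 2-year PFS, or 1/11.9 = 8.4% of that arm's planned events. This is a maximum: a patient who dies or has distant disease recorded within 2 years counts after all, only later.

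**4. How many such patients?** Pool the two sized series: 47 + 65 = 112 patients, 0 progressions. The exact two-sided 95% upper limit is 1 − 0.025^(1/112) = 0.032, or 3.2%. Applied to the arm: 0.032 × 119 = 3.9. The range is 0 to 4 of 119, with a point estimate of 0.

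**5. Which failures are uncounted, and where.**

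| Failure | Counted as written? | Arm affected |
|---|---|---|
| Growth of primary or loss of resectability before surgery | No | Mainly NAC, which has the planned window |
| New metastases before surgery | Unclear; could be recorded as distant recurrence | Mainly NAC |
| Metastases found at surgery, macroscopically incomplete resection | Not clearly | Both |
| Recurrence after resection, death | Yes | Both |

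The third row can pull the other way. The cited margin figures leave 100 − 94 = 6% not free with NAC and 100 − 89 = 11% in control. A positive margin is not a macroscopically incomplete resection, so these figures cannot be inserted as event rates. They do show that uncounted failures at surgery could be more frequent in control.

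**The case against.** The best defence is that the name of the endpoint shows the intent, the sentence is loosely worded, and new metastases before surgery would in practice be entered as distant recurrence. The full protocol, which is not shown, may also say more. The point about metastases partly stands. It does not cover growth of the primary or loss of resectability, and the published sentence is an explicit event list.

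Three stronger readings are tempting and are not supported:

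- **A known bias of several points towards NAC.** A reader might take "4.3% of patients that received NAC required emergency surgery due to obstruction during preoperative treatment" as about 5 of 119 uncounted failures (0.043 × 119 = 5.1), or treat the 3.2% limit as the likely rate, and conclude that 3 to 4 points of the 15-point target are artefact. But surgery for obstruction is not progression, and such a patient may be completely resected. The 3.2% is the top of an interval around zero observed events. Neither calculation sets control-arm failures at surgery against the NAC count.
- **An advantage to NAC from later surgery alone.** One can model an event-free wait in each arm and obtain a PFS difference with no true benefit. That requires assuming zero preoperative hazard and a control waiting time that the article does not give.
- **Exclusion of progressing patients through eligibility.** The criterion "All patients who undergo elective surgery with curative intention" could be read as depending on what happens after randomisation. The line goes on to describe the operative approach, Patient identification and consent applies the criteria before assignment, and the analysis keeps everyone randomised. No text permits later exclusion.

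**Conclusion.** The definition is wrong for this design and should be corrected before the primary analysis. Following it literally leaves preoperative progression of the primary, loss of resectability and disease-related failure of complete resection outside the primary endpoint in both arms.

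The preoperative part of the omission tends to favour NAC, because only that arm has a planned treatment window of about 13 weeks with the tumour in place. The part that arises at surgery affects both arms and may offset some of this. The net size is undetermined. The cited series are compatible with 0 to 4 affected NAC patients of 119, each worth at most about 0.8 points, against roughly 12 planned NAC events. This assumes that those series resemble the trial's patients, and the per-patient figure assumes that an affected patient has no other event within 2 years.

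**What to change.** Define the PFS event in both arms, timed from randomisation, as the first of:

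- disease progression before resection, including new metastases or loss of resectability;
- metastases found at surgery, or macroscopically incomplete resection;
- local or distant recurrence after resection;
- death from any cause.

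Add a sensitivity analysis that counts preoperative progression only where it prevented complete resection. It is needed because the restaging CT is planned only in the NAC arm, so progression visible on that scan would be found earlier there than in control. The eligibility wording needs no change for this point.

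Cost: the change adds no patients, visits or scans and does not alter treatment. The post-NAC CT is already planned. Findings at surgery should be in the operative and pathology records, although the article does not say whether macroscopic completeness is a recorded field. NAC-arm PFS may look slightly less favourable. With more than 100 patients enrolled by July 2023 in an open-label trial, the change should be a dated amendment made without reference to outcomes by arm.
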